# Safety and effectiveness of standardized exercise training in patients with pulmonary hypertension associated with heart failure with preserved ejection fraction (TRAIN-HFpEF-PH): study protocol for a randomized controlled multicenter trial

**DOI:** 10.1186/s13063-023-07297-x

**Published:** 2023-04-19

**Keywords:** Exercise training, Heart failure with preserved ejection fraction, Pulmonary hypertension, Study protocol, Randomized controlled trial

## Abstract

**Background:**

Left heart failure (HF) is characterized by an elevation in left-sided filling pressures, causing symptoms of dyspnea, impairing exercise capacity, and leading to pulmonary venous congestion and secondary pulmonary hypertension (PH). There is an increased incidence of PH associated with left heart disease, particularly with heart failure with preserved ejection fraction (HFpEF-PH). Treatment possibilities in HFpEF-PH are non-specific and very limited, thus additional pharmacological and non-pharmacological therapeutic strategies are needed. Various types of exercise-based rehabilitation programs have been shown to improve exercise capacity and quality of life (QoL) of HF and PH patients. However, no study focused on exercise training in the population of HFpEF-PH. This study is designed to investigate whether a standardized low-intensity exercise and respiratory training program is safe and may improve exercise capacity, QoL, hemodynamics, diastolic function, and biomarkers in patients with HFpEF-PH.

**Methods:**

A total of 90 stable patients with HFpEF-PH (World Health Organization functional class II–IV) will be randomized (1:1) to receive a 15-week specialized low-intensity rehabilitation program, including exercise and respiratory therapy and mental gait training, with an in-hospital start, or standard care alone. The primary endpoint of the study is a change in 6-min walk test distance; secondary endpoints are changes in peak exercise oxygen uptake, QoL, echocardiographic parameters, prognostic biomarkers, and safety parameters.

**Discussion:**

To date, no study has investigated the safety and efficacy of exercising specifically in the HFpEF-PH population. We believe that a randomized controlled multicenter trial, which protocol we are sharing in this article, will add important knowledge about the potential utility of a specialized low-intensity exercise and respiratory training program for HFpEF-PH and will be valuable in finding optimal treatment strategies for these patients.

**Trial registration:**

ClinicalTrials.gov NCT05464238. July 19, 2022.

**Supplementary Information:**

The online version contains supplementary material available at 10.1186/s13063-023-07297-x.

## Background

Pulmonary hypertension (PH) associated with left heart disease (LHD-PH) is a growing health problem with high morbidity and mortality [1–3]. Among the various PH groups, LHD-PH is the most common form and accounts for 50–80% of all cases [1, 4–8]. The estimated prevalence of PH in HF varies depending on the method of pulmonary arterial pressure (PAP) measurement, the definition of PH, the populations studied, and the type of HF. In heart failure with reduced ejection fraction (HFrEF), PH frequency is 40–75%, as assessed by right heart catheterization (RHC) [6, 9–11]. The precise prevalence of PH associated with heart failure with preserved ejection fraction (HFpEF-PH) is still unclear. Most of the data are based on echocardiographic signs, where PH prevalence in HFpEF ranges between 52 and 83% [12, 13]. In the invasive hemodynamic assessment study, among 618 HFpEF patients, 355 (57.4%) were diagnosed with PH, and 75 (21.1%) of them had combined post- and pre-capillary PH (CpcPH) [11].

Any type of left HF is characterized by an elevation in left-sided filling pressures, causing symptoms of dyspnea [14], impairing exercise capacity [15], and leading to pulmonary venous congestion and secondary post-capillary PH. Across the spectrum of LHD, increased PAP and pulmonary vascular resistance (PVR) are related to higher disease burden and worse outcomes [16–18].

Targeted medication therapy for pulmonary arterial hypertension (PAH) and chronic thromboembolic pulmonary hypertension (CTEPH), including drugs interfering with the endothelin, nitric oxide, and prostacyclin pathways, has evolved progressively in the last decades, with increasing evidence for efficacy [1, 19, 20]. However, these drugs are not recommended in patients with LHD-PH [1, 3]. Conventional HF treatments (medical/interventional) currently remain the only therapies for these patients [1, 4, 21]. Although HF syndrome covers both, HFrEF and HFpEF, these disorders have some differences in pathophysiology, clinical characteristics, hemodynamics, cardiopulmonary interaction, and response to therapy [22–24]. While pharmacological treatments are well-established in HFrEF, the same strategies could not be convincingly proven to be effective in HFpEF [21] with the recent exception of sodium-glucose cotransporter-2 (SGLT2) inhibitors case [25, 26].

In patients with HFpEF and HFpEF-PH medication therapy options remain limited—SGLT2 inhibitors, diuretics, and treatment of comorbidities are recommended [1, 21, 25, 26]. Therefore, there is a high need for additional therapeutic strategies to improve symptoms, exercise capacity, health-related quality of life (QoL), and prognosis in these patients.

The ESC/ERS 2022 guidelines recommend complex treatment of PAH, consisting of disease-targeted and supportive medical therapy, together with non-pharmacological general measures, including supervised exercise training [1], but there are no evidence-based recommendations for the exercise therapy of LHD-PH.

Different exercise-based rehabilitation programs have already been shown to improve the physical capacity and health-related QoL of PH patients [27–33]. Most of the previous trials enrolled PAH and CTEPH patients only, excluding post-capillary PH, which is pathognomonic for LHD-PH. Standardized low-intensity exercise and respiratory training programs also demonstrated an increase in exercise capacity, lower limb muscle strength, health-related QoL, and hemodynamics in PAH and CTEPH patients; LHD-PH was an exclusion criterion in all previous studies [30, 31, 33–36].

Properly designed exercise interventions for HF patients demonstrated improvement in physical capacity, health-related QoL, and risk reduction of all-cause and HF hospitalizations [37–42]. Although HFrEF patients were predominant in the largest HF exercise training trials, several systematic reviews and meta-analyses have focused specifically on HFpEF, and confirmed the positive impact of exercising on functional capacity in HFpEF, as indicated by improved peak oxygen uptake (VO_2_peak), 6-min walk test distance (6-MWD), and health-related QoL [42–47]. The number of HFpEF-PH patients in previous HFpEF exercise training trials remains unclear [48], and none of the previous studies focused specifically on HFpEF-PH.

This study is sought to investigate whether a standardized exercise training program is safe and tolerable and may improve exercise capacity, quality of life, hemodynamics, diastolic dysfunction, and biomarkers in patients with HFpEF-PH. We used the SPIRIT Checklist when writing our manuscript [49].

## Methods/design

### Study design

This study is designed as a prospective, randomized (1:1 randomization), controlled, parallel-group, superiority, multicenter trial in patients with invasively confirmed HFpEF-PH.

The total duration of the study is planned for 3 years (Q1 2023 to Q4 2025). The follow-up of individual subjects will be performed until the last patient’s last visit. The study is registered on ClinicalTrials.gov (identifier—NCT05464238). A summary of the protocol is provided in Table 1.

**Table 1 Tab1:** The World Health Organization trial registration data set: structured summary

Data category	Information
Primary registry and trial identifying number	ClinicalTrials.gov Identifier: NCT05464238
Date of registration in primary registry	July 19, 2022
Secondary identifying numbers	2019-04ET
Source(s) of monetary or material support	Heidelberg University
Primary sponsor	Heidelberg University
Secondary sponsor(s)	N/ A
Contact for public and scientific queries	[name] [contact] [name] [contact]
Public title	Safety and effectiveness of standardized exercise training in patients with pulmonary hypertension associated with heart failure with preserved ejection fraction
Scientific title	Implementation, safety, tolerability, and effect of exercise and respiratory training on 6-min walking distance in patients with pulmonary hypertension and heart failure with preserved ejection fraction (HFpEF): a randomized controlled multicenter trial in European countries
Countries of recruitment	Germany, Lithuania
Health condition(s) or problem(s) studied	Efficacy and safety of exercise and respiratory training for patients diagnosed with pulmonary hypertension associated with heart failure with preserved ejection fraction (HFpEF)
Intervention(s)	Active Comparator: Exercise rehabilitation Placebo Comparator: Standard treatment (waiting group)
Key inclusion and exclusion criteria	**Inclusion criteria:**
	- Female and male patients ≥ 18 years
	- WHO/NYHA functional classes II–IV
	- PH with HFpEF diagnosed by right heart catheterization
	- Left ventricular ejection fraction ≥ 50%
	- Patients receiving optimized therapy including intensified treatment with diuretics and who have been stable for 1 month before entering the study
	- Except for diuretics, medical treatment should not be changed during the study period
	- Able to understand and willing to sign the informed consent form
	**Exclusion criteria:**
	- Pre-capillary pulmonary hypertension
	- Congenital or acquired severe valvular diseases
	- Walking disability
	- Subject who participates in an interventional study during the course of this study
	- Severe lung disease
	- Active myocarditis, unstable angina pectoris, exercise-induced ventricular arrhythmias
	- Hemoglobin concentration less than 75% of the lower limit of normal
	- Systolic blood pressure < 85 mmHg
	- Pregnancy or lactation
	- History or suspicion of inability to cooperate adequately
Study type	Interventional, multicenter trial; intervention model description: randomized, controlled, parallel-group with crossover of the control group; masking: single (outcomes assessor); primary purpose: treatment
Date of first enrolment (estimated)	February 1, 2023
Target sample size	90
Recruitment status	Not yet recruiting
Primary outcome(s)	Changes in 6-min walking distance (time frame: baseline to 15 weeks)
Key secondary outcomes	Changes in peak exercise oxygen uptake, quality of life, echocardiographic parameters, natriuretic peptides (time frame: baseline to 15 weeks)

### Randomization and blinding

The distribution of patients to the different groups will be performed by block randomization. Group allocation will be provided in sealed envelopes, which will be prepared for each participating center by the study coordinator at Heidelberg University. Blocks for block randomization will be medium size to allow a balanced randomization sequence over time. Sites that only include a very small amount of patients may lead to a minimally unbalanced patient number. Block sizes will be the same for all centers, leading to several randomization/allocation blocks in high recruiting centers. Upon inclusion, the participants will be randomly designated to the intervention (training) or conventional (control) group. Allocation concealment will be ensured, as envelopes will not be unsealed until the patient has been recruited into the trial.

The participation in this rehabilitation program is voluntary. Participants may terminate their participation at any time.

According to the eligibility criteria, the patient should be receiving optimized and ≥ 1 month of stable treatment before inclusion in the study. Thus, we expect that the need for medication changes during the 15-week follow-up period will be minimal. However, the dosage of diuretics is permitted to be changed, and other pharmacological and non-pharmacological treatments will not be prohibited, if the treating physicians decide this to be clinically necessary. Participation in another interventional study is prohibited during the 15-week follow-up period.

Cardiologists, pulmonologists, and PH experts, blinded to the patients’ allocation groups, will perform and interpret examination tests (6-min walking test, cardiopulmonary exercise test, echocardiography, right heart catheterization, cardiac magnetic resonance imaging). Study data analytics will also be blinded to the patients’ allocation groups until the entire analysis has been completed.

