### Population sampling

Candidate patients will be selected from European pulmonary hypertension centers (a list of study sites can be found at ClinicalTrials.gov), which will be continuously updated. To achieve an adequate number of enrolled participants, healthcare professionals at involved European PH centers, as well as national associations of PH patients, will be informed about the ongoing study and the opportunity to take part in it. The diagnosis of HFpEF-PH will be established according to the ESC/ERS guidelines [1, 3, 21]. Patients will be screened before their baseline visit regarding the inclusion and exclusion criteria (days − 28 to − 1) (Table 2). After 15 weeks, patients of the control group will be offered to participate in the training program (waiting-group design). All patients will visit the clinic for pre-study screening on days − 28 to − 1 (visit [V] 1), at baseline (BL) at day 1 (V2), and week 15 (V4).

**Table 2 Tab2:** Patient eligibility criteria

Inclusion criteria	Exclusion criteria

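### Within-centre blocks of apparently one fixed size, with allocations that site staff can see, do not support the claim that sealed envelopes ensure concealment

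*Protocol article*

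**What the plan says.** All the randomization text is in the Protocol article, section Randomization and blinding.

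- Mechanism: "Group allocation will be provided in sealed envelopes, which will be prepared for each participating center by the study coordinator at Heidelberg University".
- Block size: "Blocks for block randomization will be medium size to allow a balanced randomization sequence over time". No number is given.
- Uniformity: "Block sizes will be the same for all centers, leading to several randomization/allocation blocks in high recruiting centers". The same section expects some sites to recruit very few patients.
- Concealment: "Allocation concealment will be ensured, as envelopes will not be unsealed until the patient has been recruited into the trial".

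Three other places bear on whether staff can see the allocations. Table 1 (study type) gives masking of the outcome assessor only. Under Interventions, the training arm begins with roughly three weeks in hospital, and the control arm gets no training for 15 weeks. Randomization is 1:1 (Study design).

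**The concern.** A sealed envelope hides the next allocation only if the allocations already opened do not give it away. In a 1:1 permuted block of known size, once one arm has its full quota the rest of the block must go to the other arm. Staff at a centre know who went into hospital for training and who did not, so they can keep count. The reason given for concealment, that the envelope stays sealed, does not address this.

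What is at stake is selection at enrolment. Some eligibility items in Table 2 call for judgement, such as expected cooperation, orthopaedic limits to exercise and whether treatment is likely to change. The screening window of days -28 to -1 leaves some room to time an enrolment. A recruiter who knows the next allocation could, without intending harm, enrol a more motivated patient when training is next. The baseline-adjusted ANCOVA would correct for a difference in baseline walking distance, but not for traits it does not contain.

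**Working it through.** **The plan's own figures.** The article gives no figure for predictability. The only plan number used here is the total of 90, and it reproduces: for 35 m, SD 50 m and two-sided alpha 0.05, the t-test has power 0.844 at 37 and 0.853 at 38 per group. Then 38/(1 - 0.15) = 44.7, rounded up to 45 per group and 90 in total. Nothing below changes it.

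**Inputs.** 1:1 allocation and separate envelopes per centre are stated. The block size is an assumption: the article says only that it is medium, so 4, 6, 8 and 10 are shown. A further assumption is that someone tracks every allocation at the centre and knows or has inferred the size.

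**Complete blocks of one known size.** For block size 2m, the expected number of allocations fixed by the earlier ones is 2m/(m+1), so the share is 1/(m+1). Enumerating all permuted blocks gave the same values, and also the success rate of always guessing the arm that is behind in the block.

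| Assumed size | Determined per block | Share | Of 90 | Best guess right |
|---|---|---|---|---|
| 4 | 4/3 = 1.33 | 33% | 30 | 71% |
| 6 | 6/4 = 1.50 | 25% | 22.5 | 68% |
| 8 | 8/5 = 1.60 | 20% | 18 | 67% |
| 10 | 10/6 = 1.67 | 17% | 15 | 65% |

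An unpredictable sequence gives 0% determined and 50% guessed right.

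**Incomplete blocks at smaller sites, size 6.** There are 20 possible blocks. The fourth allocation is determined only if the first three agree (2 of 20 = 0.1), the fifth if three of the first four agree (8 of 20 = 0.4), and the sixth always (1.0). The sum is 1.5, as in the table.

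- 4 patients: 0.1/4 = 2.5% (2.4% in simulation).
- 9 patients: one full block plus three undetermined places, 1.5/9 = 17%.
- 45 patients: seven full blocks plus three places, 7 × 1.5/45 = 23%.

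Multiplying the full-block share by 90 is therefore a ceiling, approached only where centres run several blocks. The dilution depends on the size: with size 4, a 4-patient site completes a block and the share is already 33%.

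**Effect of varying the size.** This was simulated for a 24-patient site (3,000 runs), with a guesser who knows the set of sizes but not their order.

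| Scheme | Determined | Best guess right |
|---|---|---|
| Fixed 6 | 25% | 68% |
| Random 4/6 | 5% | 69% |
| Random 4/6/8 | 2% | 67% |

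Mixing sizes removes nearly all the certain allocations but hardly changes the success of guessing.

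**The case against.** **One fixed size is not stated.** The sentence compares centres, and a common set of varying sizes would also satisfy it. That stands as a caveat. A single size remains the natural reading, and nothing in the section describes variation within a centre.

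**The size may already be withheld.** The article does not print it and does not say sites are told. That stands too: staff would have to infer it. Size 4 also fits the word medium poorly; without it the range is about 15 to 22 of 90.

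**Predictability is not bias.** Correct. The figures count allocations that could be foreseen. They say nothing about whether anyone would act on that, and the documents give no basis for a bias in metres. Blinded assessors and baseline adjustment give partial protection, but neither acts on who is enrolled when.

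**A stronger reading about baseline effort.** Because allocation follows inclusion ("Upon inclusion, the participants will be randomly designated to the intervention (training) or conventional (control) group") and screening precedes the day-1 baseline visit, a reader might infer that patients know their group before walking the baseline test. The documents do not support this. Population sampling lists the visits without placing randomization among them, the timeline figure is not shown, and the order of envelope opening and baseline testing is detail that an article leaves to the full protocol. Silence here is not an error.

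**Conclusion.** The point holds in a limited form. In a trial whose allocations are visible to site staff, centre-specific envelopes with blocks of apparently one size do not by themselves justify saying that concealment will be ensured. At most about 17% to 33% of allocations (15 to 30 of 90, for assumed sizes 10 to 4) are determined in advance. That ceiling requires a known or inferred size, completed blocks and someone keeping count. It should not be read as an expected number, nor as evidence that selection will occur. Exposure is concentrated at high-recruiting centres, which the article itself expects to run several blocks. The distribution of patients over sites is not given, so no trial-wide figure below the ceiling can be calculated.

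**What to change.** For envelopes not yet issued, the study coordinator should generate each centre's list with block sizes that vary at random within the centre, for example 4, 6 and 8, and should not disclose the sizes to sites. The concealment sentence should then rest on both features: envelopes sealed until recruitment, and block sizes that vary and are unknown to recruiting staff. If the full protocol already does this, one clarifying sentence is enough.

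The cost is a new set of centrally prepared lists. Sample size and visits stay as they are. Two limits should be acknowledged:

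- Best-guess success stays near 67%, so the change removes near-certainty, not every advantage from counting.
- Imbalance at a small site can be slightly larger. An unfinished block can be out by half its size: 3 with a fixed size of 6, and up to 4 when 8 is in the mix (no increase if the present size is 8 or 10). The planned analysis cannot be relied on to absorb this. Under Statistical analysis, the primary ANCOVA names only the baseline value as covariate, and centre effects are examined only if numbers permit.

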### Population sampling

Candidate patients will be selected from European pulmonary hypertension centers (a list of study sites can be found at ClinicalTrials.gov), which will be continuously updated. To achieve an adequate number of enrolled participants, healthcare professionals at involved European PH centers, as well as national associations of PH patients, will be informed about the ongoing study and the opportunity to take part in it. The diagnosis of HFpEF-PH will be established according to the ESC/ERS guidelines [1, 3, 21]. Patients will be screened before their baseline visit regarding the inclusion and exclusion criteria (days − 28 to − 1) (Table 2). After 15 weeks, patients of the control group will be offered to participate in the training program (waiting-group design). All patients will visit the clinic for pre-study screening on days − 28 to − 1 (visit [V] 1), at baseline (BL) at day 1 (V2), and week 15 (V4).

**Table 2 Tab2:** Patient eligibility criteria

Inclusion criteria	Exclusion criteria
1. Female and male patients ≥ 18 years 2. WHO functional classes II–IV 3. PH confirmed by RHC, showing *mPAP* > *20 mmHg at rest*; HF confirmed by invasive measurements, when *mPAWP* ≥ *15 mmHg* or *LVEDP* ≥ *16 mmHg* at rest and/or *PAWP* ≥ *25 mmHg* during exercise and/or *PAWP* > *18 mmHg* after the fluid challenge test 4. Preserved left ventricular ejection fraction > 50% *(measured by echocardiography or MRI)* 5. A patient received optimized and for ≥ 1 month stable therapy, including adequate treatment with diuretics 6. Except for diuretics, medical treatment should not be expected to change during the study period 7. Able to understand and willing to sign the informed consent form	1. Pre-capillary pulmonary hypertension *(group I, group III, group IV, group V, according to the ESC/ERS PH guidelines)* 2. Congenital or acquired severe valvular diseases *(severe aortic stenosis or insufficiency, severe mitral valve stenosis or insufficiency)* 3. Active myocarditis, unstable angina pectoris, exercise-induced ventricular arrhythmias, active liver disease, porphyria, or elevations of serum transaminases > 3 × ULN (upper limit of normal) or bilirubin > 1.5 × ULN 4. Severe lung disease: FEV1/FVC < 0.5 and total lung capacity < 60% of the normal value 5. A subject who participates in an interventional study during this study 6. Walking disability or other orthopedic limitations to exercise 7. Hemoglobin concentration less than 75% of the lower limit of normal 8. Systolic blood pressure < 85 mmHg 9. Pregnancy or lactation 10. History or suspicion of inability to cooperate adequately

*FEV1* forced expiratory volume in the first second, *FVC* forced vital capacity, *LVEDP* left ventricular end-diastolic pressure, *mPAP* mean pulmonary arterial pressure, *mPAWP* mean pulmonary arterial wedge pressure, *PH* pulmonary hypertension, *RHC* right heart catheterization, *WHO* World Health Organization

